#### *8.6.5. Economic evaluation outcomes*

1. Patients costs of receiving the intervention
2. Patients costs related to treatment of the primary disease, readmission or death
3. The costs of the health care system of providing the intervention
4. The costs of the health system of treating the primary disease and anaemia, as well as treatment of readmissions or costs related to fatalities

For more detailed definitions of intervention costs outcomes, see section 9.8, 'Economic Evaluation sub-Study', page 55.

## 8.7. PARTICIPANTS TIMELINE

### 8.7.1. Overview Study Phases

The study plan and schedule of assessment is provided in Table 1: Study treatment and phases, Page 14 and Table 2: Study Design and Schedule of Assessment, Page 15, and Figure 1: Flow of Participants, page 17.

It consists of an in-patient pre-study screening period while the patient is acutely ill (approximately - 4 to 0 days before enrolment) followed by a screening and enrolment visits during the convalescence phase in the hospital, just prior to discharge. It will be during this enrolment visit when the children become formal study participants (t=0). They will also be provided with artemether-lumefantrine (AL) (Coartem®) during this time (both arms) as soon as the child can take oral medication, taking any pre-enrolment doses of AL into account that may already have been provided by the hospital as part of standard care. The child will then be seen again at 14 days, when they will be allocated to one of the two study arms and receive their first course of active PMC or placebo. The subjects will be visited again at home at 6 and 10 weeks after enrolment to be administered the second and third course of PMC. These home visits will be for drug administration purposes and vital registration only, not for clinical assessment. The PMC period ends at 14 weeks, i.e. 4 weeks after the third PMC course. They will then be followed up for an additional 12 weeks through passive follow-up and then seen at 26 weeks for an end of study assessment. Subject's parent or guardian will be instructed to return his/her child to the study clinic for evaluation free of charge at any time their condition warrants medical attention during the 26 weeks follow-up period after discharge.

### 8.7.2. Visit 1: Pre-screening

Parents / guardians of children who fulfil the pre-screening eligibility criteria (see section 8.4.1, page 26) will be informed about the study by the hospital or study staff. Consent will not be obtained at the acute stage of the illness but a few hours or days later when the child has recovered and is able to take oral medication (see section 8.7.3, below). This provides a time window for the parents or guardian to reflect on the study and discuss it with family members and study staff.

Pre-study screening will be done by hospital staff or study staff. No study specific information or study samples will be collected in this pre-study screening period. However, study staff will be asked to keep any leftover blood volume of routine samples that would otherwise be discarded (e.g. for blood-group typing and cross-matching) in the fridge until consent is obtained in visit 2 (see below), including malaria smears taken on enrolment. The role of the study team during this period is to review the diagnosis and ensure that the potential study participants get standard care for severe malarial anaemia.

Each pre-screened subject will be assigned a pre-screening number in sequential order by the hospital regardless of whether they fulfil the pre-screening eligibility criteria. Data will be recorded on a pre-screening log that will be kept in the investigator's site file. One pre-screening log will be kept per hospital. This record will be used to report how many patients were pre-screened and how many were eventually recruited in the study to establish that the study population was selected without bias. This screening log will not contain names or other identifying information.

### 8.7.3. Visit 2: Screening interview and consent & Enrolment

#### 8.7.3.1. Screening & Consent

The parents of the children will be approached for a screening interview as soon as the child is sufficiently recovered to take oral medication (i.e. after completion of the blood transfusion and the standard parenteral artesunate medication [if any is indicated]). This is typically within 24 to 48 hours following admission to the hospital. During this interview, consent will be sought from the parents or guardian and if consent is granted, the eligibility criteria for inclusion into the study will be assessed (for the criteria, see section 8.4.2, page 26). For further details regarding the consent procedure see also section on consent procedure, section 11.4, page 57.

#### 8.7.3.2. Screening log

The investigator will keep a subject screening log for all subjects considered for enrolment regardless of whether they were enrolled, which, combined with the pre-screening log will be used to establish that the study sample was selected without bias. This screening log will not contain names or other identifying information.

#### 8.7.3.3. Assignment of study IDs

Screened subjects who meet all eligibility criteria will be issued a study subject number during this visit. Once issued the study subject number they will be considered as 'enrolled.' This number is the subject's unique identifier and used to identify the subject on the CRFs. Subject numbers will be assigned strictly sequentially as subjects enter the study. Once a number has been assigned no attempt will be made to use that number again, for example if a subject discontinues or is a screening failure.

#### 8.7.3.4. Clinical assessment:

After consent is obtained and the subject's eligibility is confirmed, the subject's demographic data will be recorded in the CRF, and all relevant clinical information, including the previous and current medical history, and laboratory information copied from the hospital's clinic and laboratory notes to the CRF (see CRF for details). A further clinical examination (including anthropometrics) will be performed and a medical history taken that will serve as the baseline examination and captured on the CRF.

#### 8.7.3.5. Baseline Laboratory Measurements:

*As part of standard of care:* Children with severe anaemia are expected to have the following tests done as standard of care before blood transfusion: Malaria smear or RDT, haemoglobin concentration, blood smear to type the anaemia, blood cultures (if patient is febrile and facilities are available), complete blood count haemogram (subject to availability of automated analysers). In addition they are expected to have a blood group and cross match test with donor blood as part of the blood transfusion process. After completion of the blood transfusion, a post transfusion haemoglobin concentration is taken. If the patient was suspected to have malaria, a repeat malaria smear or RDT is often taken to evaluate whether the parasitemia has been cleared.

We shall record all these laboratories results and any others tests results such as urinalysis and radiological results that might have been done as part of standard of care. During the pre-study screening period the study team shall support the hospital to facilitate the routine use of these tests

and the recording of clinical and laboratory information on the clinical and laboratory forms and hospital registers to ensure they are available to the study team once the patient is enrolled into the study.

*Study specific samples:* In addition to the standard of care tests, a venous blood sample will be taken (3 ml) through the existing cannula where possible (in which case no additional ‘prick’ will be required). This will be used for red cell morphology, and human and parasite genetics including pheno/genotyping for polymorphisms selected for malaria or other causes of severe anaemia. The pheno/genotypes of primary interest are those for hemoglobinopathies (sickle cell disease and thalassemia) and G6PD deficiency. Blood will also be stored for genotyping of the malaria parasite (and again at initiation of PMC [visit #4, section 8.7.5, page 39] and during unscheduled sick child clinic visits for clinical malaria episodes, and the final post-PMC [visit #7, section 8.7.7, page 40]).

*HIV testing or collection of information on HIV-exposure* (i.e. maternal HIV status) will not be done as a study specific procedures, but the information will be copied from the clinical and laboratory hospital records of patients, including information on the maternal HIV status, where available, or the HIV-status will be obtained following provider initiated testing and counselling (PITC) procedures that are part of routine in-hospital care. Where required the study will support the hospital infrastructure needed to generate this information for the study to ensure this information is available for all study participants.

#### 8.7.3.6. Location of household and issuance of study ID card

A detailed route description to locate the participant’s household, including sketching a map, if needed, will be recorded, to aid the planned PMC treatment follow up visits at home. Lastly, a subject’s identification card will be issued.

#### 8.7.4. Visit 3: AL treatment in hospital/discharge

The first study dose(s) of the first course of AL drugs will be administered to the child whilst in hospital. These will be directly supervised by study staff. Any AL doses provided as part of routine in-patient care by hospital staff prior to study enrolment will also be recorded to ensure that children do not receive more than 6 cumulative doses of AL over 3 days. Some questions about patient’s costs will also be asked during this visit (see section 9.8, ‘Economic Evaluation sub-Study’, page 55)

#### 8.7.5. Visit 4: Randomisation and 1st PMC treatment visit

Randomisation will take place during visit 4, 2 weeks post enrolment, by opening a single concealed envelope containing the study drugs which will be pre-packed by the study pharmacist (for full details about the randomisation and blinding, see section 8.10, ‘Assignment of interventions and blinding’, page 42. The first PMC treatment visit can take place at home or in the clinic, subject to local circumstances. The first dose of medication will be observed, and the family will be given the study drug to administer at home on the subsequent 2 days. Prior to drug administration, a finger prick will be taken for Hb determination and a filter paper blood spot for parasite genetics.

#### 8.7.6. Visits 5 and 6: 2nd and 3rd PMC treatment visits

The 2nd and 3rd PMC treatment will be given 6 and 10 weeks following enrolment. These treatment visits will take place at home by a home visitor who will administer the first day of PMC study drugs, and will give the family the rest of the dose to be administered at home. If children are found to be

ill during these home-visits they will be referred to the study clinic for further evaluations as part of the unscheduled visits described below (section 8.7.8, page 40). The presence and use of insecticide treated nets will be recorded during these home visits.

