#### 9.2.2. Baseline characteristics

Descriptive statistics of baseline characteristics, overall and by treatment group will be provided in a table consisting of parameters collected prior to randomisation. No statistical comparisons

will be made between the groups, but any differences between groups at baseline which are also associated with the outcome variable will be taken into account in subsequent analysis.

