### *9.2.5. Assessment of efficacy*

#### *9.2.5.1. Primary analysis*

Primary analysis will be by intention to treat, and include all primary endpoint events to capture the potential effect of PMC on reducing first and repeat events. The associated statistical null hypothesis is that there is no difference between the treatment groups in the distribution of the incidence rate of the primary endpoint, and the alternative hypothesis is that there is a difference between treatment groups.

The follow-up time will be measured as the time in days from the date of randomisation to the end of follow-up, death or drop-out. The incidence rate will be calculated per arm and the rate ratio (RR, PMC to placebo) and 95% confidence intervals (CI) estimated using Poisson regression models, stratified by country, with treatment (as randomized) as the only co-variate. The results will be expressed as the relative rate reduction (RRR) (95% CI) calculated as 100 multiplied by (1–RR).

In addition to the final analysis, the primary statistical hypothesis will be tested in an interim analysis when approximately half of patients are recruited as described in more detail in section 9.5.1.2, page 49.

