#### 9.2.5.2. Subgroup analysis

We will use stratified analysis to assess to what extent the effect of the intervention on the primary outcome is influenced by the following potential effect modifiers:

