##### *Transmission variables*

8. Malaria transmission intensity: moderate vs high. PMC is hypothesized to be more effective in children living in high transmission areas as the relative contribution of malaria to post-discharge morbidity may be higher and thus more malaria related events can be prevented.
9. Residence: Urban vs rural. PMC is hypothesized to be more effective in children living in rural areas which have higher malaria transmission.
10. Season: Terciles, based on average rainfall during the 6 month study period for each child. PMC is hypothesized to be more effective in malaria transmission season when more potential malaria related events can be prevented.
11. ITN use vs non-use. PMC is hypothesized to be more effective in non ITN users as more potential malaria related events can be prevented.

12. Study Site: about 7 sites, as used in the stratification. PMC is hypothesized to be more effective in children living in high transmission sites as the relative contribution of malaria to post-discharge morbidity may be higher and thus more malaria related events can be prevented.

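### ITN use is a planned effect modifier, but the protocol schedules its recording only at weeks 6 and 10, after randomisation; unless the CRF asks earlier, subgroup 11 rests on a post-randomisation variable

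*Protocol*

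**What the plan says.** Protocol 9.2.5.2 plans stratified analyses to see how far the effect on the primary outcome is "influenced by the following potential effect modifiers". Item 11, under the transmission variables, reads "ITN use vs non-use. PMC is hypothesized to be more effective in non ITN users as more potential malaria related events can be prevented".

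The timing of net recording is stated once, in 8.7.6 on visits 5 and 6: "The presence and use of insecticide treated nets will be recorded during these home visits". The same section places those visits in time: "PMC treatment will be given 6 and 10 weeks following enrolment".

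Allocation comes earlier. Section 8.7.5 states: "Randomisation will take place during visit 4, 2 weeks post enrolment". The first course is given at that visit. Primary follow-up starts there too, since 9.2.5.1 says: "The follow-up time will be measured as the time in days from the date of randomisation to the end of follow-up, death or drop-out".

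Nets are not mentioned in the enrolment procedures (8.7.3), the visit 4 description (8.7.5), the visit 7 description (8.7.7) or the schedule in Table 2. The other references to bed nets (3.2, 4.4, 5.2) are background. The baseline table in 9.2.2 is defined as "consisting of parameters collected prior to randomisation".

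**The concern.** A subgroup analysis of a randomised comparison is cleanest when the subgroup is fixed before allocation. Neither treatment nor outcome can then influence who belongs to which stratum. Followed as written, the protocol gives an ITN variable that fails this in two ways.

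First, a child who dies, withdraws or is lost between weeks 2 and 6 never receives an ITN value and drops out of the subgroup analysis. Death is part of the endpoint, so classification depends on surviving to visit 5.

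Second, net use can respond to illness. A family whose child is readmitted or treated for malaria in weeks 2 to 6 may obtain a net or start using one, and the child is then recorded as a user. Treatment is meant to change exactly those events, so stratum membership could lie downstream of treatment. Blinding prevents families from acting on knowledge of the allocation, but it does not close this route through illness.

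At stake are the stratum-specific rate ratios for users and non-users and the contrast between them. A variable recorded only at visits 5 and 6 would also fall outside the 9.2.2 baseline table. An analysis plan written later can choose between the two records, but it cannot recover a pre-allocation value that nobody collected.

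**Working it through.** The protocol states no figure on this point, so there is none to reproduce. The check has two parts: the order of events, and the size of the gap.

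**Order of events (weeks from enrolment)**

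- Week 2: randomisation, first course, start of primary follow-up (8.7.5, 9.2.5.1).
- Week 6: visit 5, first scheduled net record (8.7.6).
- Week 10: visit 6, second scheduled net record (8.7.6).
- Week 26: end of follow-up.

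The records come 6 − 2 = 4 and 10 − 2 = 8 weeks after randomisation. The share of primary follow-up before the first record is 4/24 = 16.7%.

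**Events before the first record**

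Inputs from 8.8.1.1 are 520 children per arm and rates of 1.152 (control) and 0.864 (PMC) per child-year. The rate is assumed constant, with no allowance for loss.

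- Control: 520 × 1.152 × 4/52 = 46.
- PMC: 520 × 0.864 × 4/52 = 35.
- Total: about 81.

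These events happen before ITN status is known. They are not all lost from the subgroup, because a child readmitted in weeks 2 to 6 and alive at visit 5 still gets a value.

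**Children with no value at all**

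For a proportion d with the event over 24 weeks at constant hazard, the expected number before week 6 is 1040 × [1 − (1 − d)^(4/24)].

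| Reason | d | Source of d | Children before week 6 |
|---|---|---|---|
| Death | 2% | assumption, low end | 3.5 |
| Death | 8% | assumption, high end; 4.1 reports 8% by 6 months post-discharge in Malawi | 14.4 |
| Loss | 10% | allowance in 8.8.1.1 | 18.1 |

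Adding deaths and losses gives 3.5 + 18.1 = 21.6 (2.1% of 1040) to 14.4 + 18.1 = 32.5 (3.1%). The sum treats the 10% allowance as excluding deaths; if it includes some, the total is smaller. Section 4.1 says risk is highest in the first 3 months, so a constant hazard may understate early deaths.

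**Net use changed by illness**

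The documents give no rate at which families acquire or start using nets after an illness, so this part of the bias cannot be sized.

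**The case against.** The strongest reply is that the protocol does not list its questionnaire items. Section 8.7.3.4 refers to the CRF for detail, and Appendix IX says the questionnaires are still to be designed. Other listed modifiers, such as urban or rural residence, appear in no visit description either. A reader might infer that nets are never asked about before allocation. The text does not establish that: it shows one scheduled time and is silent elsewhere. This stands, and it makes the point conditional.

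It can also be said that the protocol does not contradict itself. Item 11 fixes no measurement time, and the list was never restricted to baseline variables: it includes rainfall over the child's study period, period of assessment and dose received. Covariates for the subgroup analyses are left to the SAP. This stands too. The fault lies in the data-collection schedule and is not an inconsistency between sections.

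Home visits have a real advantage, since a net can be seen. Visit 4 may be held in clinic, where only a caregiver's report is available. At enrolment the child is an inpatient, typically 24 to 48 hours after admission, so a question about the previous night would describe the hospital. These points shape the fix but do not remove the need for a pre-allocation value.

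Two further inferences are tempting. One is that about 81 events vanish from the subgroup; they do not, because the child is lost only through death or loss before visit 5. Even for deaths, 8.7.8.2 provides a verbal-autopsy home visit whose content is not shown. The other is that 5.2 makes this subgroup central to policy. That section asks about the impact of PMC where nets and other interventions are already in use. It does not ask for a comparison of users with non-users.

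**Conclusion.** The point holds in conditional form and is worth acting on, but it is not critical. On the protocol's text, subgroup 11 would use a variable first recorded 4 weeks after randomisation. About 22 to 33 of 1040 children (2% to 3%) would have no value, and illness in weeks 2 to 6 could affect the classification of some others. This assumes that the CRF contains no earlier net question, that 24-week mortality lies between 2% and 8%, that loss is 10%, and that hazards are constant.

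The likely bias is modest. The trial is double-blind, the window is short, and few children are unclassified. The protocol itself says that its 14 subgroup analyses lack power and will be read with caution. A reader might go on to doubt the main result. Nothing here supports that: the primary intention-to-treat analysis uses treatment as its only covariate, stratified by country, and the sample size does not depend on ITN status.

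**What to change.** - Ask about usual net ownership and use at home at visit 4, before the study ID is written on the envelope or box (the moment at which 8.10.1.3 counts a child as randomised). Alternatively, ask at enrolment, worded as use at home before admission and not as the previous night.
- Add the item to Table 2 and to 8.7.5 (or 8.7.3.4 if asked at enrolment). If the CRF already contains such a question, state this in the protocol.
- Define item 11 of 9.2.5.2 on that pre-allocation value.
- Keep the visit 5 and 6 home records as descriptive data on net use during follow-up.
- For children already randomised without the item, use the visit 5 value only in a sensitivity analysis labelled as resting on a post-randomisation variable.

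The cost is one or two CRF questions at a visit that already takes place, and one line in 9.2.5.2. The downside is that, when visit 4 is held in clinic, the subgroup rests on caregiver report instead of direct observation; the retained home records let the two be compared.

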### *8.7.7. Visit 7: 6-month scheduled follow-up*

Study participants will be asked to return to the study clinic at the hospital at 6 months. Phone reminders or home visits reminders will take place prior to this visit to enhance the uptake assessment. At this visit a history will be taken and examination performed. A blood sample will be taken for malaria slides, parasite genetics and full blood count. Additional treatment for malaria and / or anaemia will be given if required. Study staff will visit the house if the family fails to present for this visit at the clinic.

### *8.7.8. Unscheduled visits (passive follow-up)*

#### *8.7.8.1. Intercurrent illness*

A passive surveillance system will be used to monitor intercurrent illnesses through study-clinics. Parents will be instructed to bring their child to the study clinic for any suspected illness. The 'chief complaint' (reason for attending the clinic during passive surveillance) and 'diagnosis' will be recorded using a standard list based on the International Classification of Disease (ICD-10) for children. Blood samples for malaria smears, parasite genetics (filter paper dried blood spots) and haemoglobin will be taken if clinically indicated (e.g. documented fever  $\geq 37.5$  °C axillary or  $>38.0$  °C rectal, or a history of fever in the last 24 hours).

